#### Waitlist

Participants in the waitlist condition will be instructed to wait for 14 weeks. After this waiting period, they will no longer take part in the study, but will be offered iCBT treatment with planned therapist feedback. If participants do not wish to receive the iCBT treatment, they will receive assistance in finding another relevant treatment if needed.

### Criteria for discontinuing or modifying allocated interventions {11b}

If an adolescent shows an increase in co-morbid depressive symptoms above the cutoff for clinical depression, or if they show signs of suicidal ideation, the clinician will contact both the participant and their legal guardians to discuss whether the participant should be discontinued from the study and receive help finding other treatment if needed. The clinician may contact the participants up to three times during the trial to investigate depression or suicidal ideation. If the participant shows increase in depressive symptoms or exhibits suicidal ideation for the third time during the treatment, the purpose of the contacts will be to discontinue the participant from the study and help them find other treatment if needed.

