#### iCBT with on-demand feedback

Participants in the on-demand feedback iCBT condition will not receive any planned contact with the therapist. However, they will have the option to contact the therapist through messages within the program and receive asynchronous support.

In both treatment conditions, the therapist may spend a maximum of 15 min giving feedback per week. While we have advised therapists to adhere to this standard time used per participant in The Internet psychiatry, we cannot fully ensure adherence to this rule as it is up to the discretion of each therapist. Since there is no evidence on what amount of therapist support is sufficient for adolescents, the allowed time spent giving feedback will not differ between the two conditions. Participant depression and suicidality will also be continuously monitored in both intervention conditions using in-session questionnaires (see section “Plans for assessment and collection of outcomes {18a}”).

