### Plans to promote participant retention and complete follow-up {18b}

If a participant is inactive (e.g., did not log in to the platform) for more than 10 days, the therapist will initially contact the participant through the chat function on the platform. The purpose of this contact is to assess the reasons for inactivity and to schedule a motivational conversation with the participant and their parents if necessary.

If the participant does not respond to the chat messages within 2 days, the therapist will contact them by telephone to assess the reasons for inactivity and schedule a motivational conversation. These conversations may last up to 45 min and aim to help the participant identify reasons for change and address potential treatment barriers.

The participant will be encouraged to continue working with the program during these conversations. However, if inactivity persists, the participant will be discontinued from the treatment and assisted in finding a more suitable treatment option.

All participants enrolled in the study will receive the post- and follow-up measures, unless they specifically decline participation in these. Therefore, even participants who do not complete the treatment will still be assessed with all measures.

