### Adverse event reporting and harms {22}

Another committee, comprising clinicians working on the project and members of the research team, will be established to monitor individual risks on a case-to-case basis. This committee will oversee screening for depression and suicidality using S-MFQ scores, and anxiety symptom severity using CAS-8. Screening will occur daily, with exceptions for holidays and weekends.

Additional negative effects will be assessed through the NEQ after the adolescent have completed 14 weeks of treatment. If any risks or harms are detected, the committee will report to the assigned clinician. It will then be the clinician’s responsibility to contact the participant, and/or their legal guardians to investigate if the participant needs additional help. All adverse events will be recorded in the trials database.

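### The rule for a third episode of worsening removes a participant from the study, although the retention section promises outcome measures to everyone enrolled

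*Protocol article*

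**What the plan says.** Section {11b} of the protocol article (criteria for discontinuing or modifying allocated interventions) has two steps. When depressive symptoms rise above the clinical cutoff or suicidal ideation appears, the clinician contacts the family "to discuss whether the participant should be discontinued from the study". At the third occurrence during treatment the step is no longer a discussion: "the purpose of the contacts will be to discontinue the participant from the study and help them find other treatment if needed".

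Section {18b} (retention and complete follow-up) sets out who is measured: "All participants enrolled in the study will receive the post- and follow-up measures, unless they specifically decline participation in these". It adds that "even participants who do not complete the treatment will still be assessed with all measures". For inactive participants the same section uses a narrower term: "if inactivity persists, the participant will be discontinued from the treatment and assisted in finding a more suitable treatment option".

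Neither section refers to the other.

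**The concern.** The only exception in {18b} is the participant's own refusal. Removal by a clinician is not an exception, yet {11b} orders it and names the study, not the treatment, as what is left. A clinician who compares the two rules could reasonably conclude that inactive adolescents stay in follow-up and worsening adolescents do not.

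If that happens, outcomes are missing because of worsening after randomisation. The loss would fall mainly in the iCBT arms, for which the monitoring is described: "Participant depression and suicidality will also be continuously monitored in both intervention conditions using in-session questionnaires". Three outcomes are affected to different degrees:

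- **MFQ:** directly, because depressive worsening is itself a trigger.
- **NEQ:** directly. Section {22} says "Additional negative effects will be assessed through the NEQ after the adolescent have completed 14 weeks of treatment", and section {20b} compares its 20 items between arms at post-treatment. Losing those who worsened would understate negative effects.
- **SCAS (primary):** indirectly, because the trigger is depression or suicidality and not anxiety. Any bias would favour iCBT.

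The maximum-likelihood mixed model in {20c} tolerates missing values but may not absorb loss that depends on worsening after baseline. Detection of individual harm is not at stake, since "All adverse events will be recorded in the trials database".

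**Working it through.** **Reading the sections together**

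| Protocol section | What it settles |
|---|---|
| {11b}, first and second episode | Leaving the *study* is discussed |
| {11b}, third episode | Leaving the *study* is the purpose of the contact |
| {18b}, inactivity | Leaving the *treatment* |
| {18b}, measurement | Everyone enrolled, unless they decline; non-completers included |
| {8} and Waitlist | Waitlist participants leave the study after the post-waitlist measures and are not measured again |
| {11d} and {20c} | Intention to treat; additional treatment does not exclude anyone from analysis |

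The waitlist rule shows that this protocol itself treats leaving the study as the end of measurement, so the literal reading of {11b} is not strained. On the other side, the heading of {11b} concerns interventions, {18b} is the only text on who is still assessed, and the intention-to-treat commitment needs the data. *Treatment* is therefore the likely intent, but the text does not say so.

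**Size under the literal reading, SCAS**

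Inputs from Sample size {14}: σ = 15, ICC = 0.6, planning difference 10 points, 112 treated, 134 analysed after attrition (45 and 89 at 1:2).

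Assumptions, not in the documents: the ICC serves as the pre-post correlation; a lost participant's true post-treatment score is 0.5 to 1 conditional SD worse than the model predicts; k = 1 to 5 participants are lost this way.

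1. Conditional SD of post given pre = 15 × √(1 − 0.6²) = 12.0, so the shortfall is 6 to 12 points.
2. Shift in the iCBT mean = k × shortfall / 112:

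| k | share of 112 | 6-point shortfall | 12-point shortfall |
|---|---|---|---|
| 1 | 0.9% | 0.054 | 0.107 |
| 3 | 2.7% | 0.161 | 0.321 |
| 5 | 4.5% | 0.268 | 0.536 |

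3. As a share of the 10-point difference: 0.054/10 = 0.5% to 0.536/10 = 5.4%.
4. Standard error of the contrast = 12 × √(1/45 + 1/89) = 2.19, and 0.536/2.19 = 0.24.
5. Losses needed for a 1-point shift: 112/12 = 9.3, so 10, up to 112/6 = 18.7, so 19.

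Step 5 describes an unlikely case. Section {10} excludes current suicidal ideation and moderate to severe depression at entry, and the rule needs three episodes within 14 weeks.

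No comparable calculation is possible for MFQ or NEQ, because the documents give no planning values for them.

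**The case against.** The strongest reply is that {18b} already decides the matter. Section {11b} says nothing about measurement, its heading limits it to interventions, and both sentences in it go on to speak of finding other treatment. On that view the word *study* is a slip with no effect. This is the likelier reading, and on it the effect is zero. It remains an inference, because {11b} uses the word twice and {18b} uses a different one.

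A second reply is that the link may sit in the full protocol or in the field guidebook mentioned in {23}. That is possible, but neither is shown. The point also concerns two stated rules that conflict, not a detail left out of a condensed article.

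Third, loss mainly in the iCBT arms cannot be fully verified. Section {22} describes S-MFQ and CAS-8 screening without naming arms, and the timeline table is not readable here. This caveat stands, although the in-session monitoring and the phrase about treatment in {11b} both point to the iCBT arms.

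Fourth, read strictly, {22} gives the NEQ only after 14 weeks of treatment, so rewording {11b} alone might not recover it. Since {20b} treats the NEQ as a post-treatment outcome, the added sentence in the fix covers it.

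Fifth, the SCAS figures rest on assumptions, and the shift uses 112 while the standard error uses 89. Using 56 and 112 throughout gives a standard error of 12 × √(1/56 + 1/112) = 1.96 and a ratio of 0.536/1.96 = 0.27, which is much the same.

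Finally, full withdrawal could be a deliberate safety choice for at-risk minors. If so, {18b} is the section that is wrong and should state the exception. The conflict needs resolving either way.

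**Conclusion.** The concern holds as a conflict in wording that costs almost nothing to remove. Confidence is medium, because the likely intent is already the right one. If {18b} governs, the effect is zero. If {11b} is applied literally, the SCAS shift is 0.05 to 0.54 points for an assumed 1 to 5 losses with a 6 to 12 point shortfall, which would not change the primary conclusion. The more direct exposure is in MFQ and NEQ, and its size is unknown. The case for acting now is that an analysis plan written later cannot recover outcomes that were never collected.

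**What to change.** In {11b}, change both mentions of leaving the study to leaving the treatment: *discontinued from the treatment* in the first rule and *discontinue the participant from the treatment* in the third-episode rule. Then add: *Post-treatment and follow-up measures are still requested unless the family declines (see {18b}).*

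The clinical decision, the limit of three contacts, the referral to other care and the family's right to decline all stay as they are. The cost is two word replacements, one sentence, and a few more questionnaire invitations through the existing REDCap system.

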### Strategies to improve adherence to interventions {11c}

To improve adherence to the intervention, the therapist will actively monitor the adolescent’s engagement with the treatment program. If an adolescent fails to engage with the program for 10 consecutive days, both the adolescent and the parents will be given the option of a motivational video call. This call will serve to explore the reasons behind the lack of participation and to assist in developing strategies to help the adolescent continue with the treatment. The motivational video call should not include any form of CBT, and will only be offered once per family.

### Relevant concomitant care permitted or prohibited during the trial {11d}

Participants are not allowed to partake in other psychotherapeutic anxiety treatments during participation, unless it is deemed unethical to prohibit such treatment, which will be assessed on a case-by-case basis. This assessment will occur during the informational video call, as well as in pre- and post-treatment questionnaires. Participants who mention seeking additional care for anxiety during the video call will be advised to only partake in one treatment at the time, unless it is deemed unethical for the participants. There are no restrictions on seeking additional non-anxiety-related care, but data on additional care utilized during the treatment period will be obtained at post-treatment.

Stable medication during participation is preferred, but we do not have the authority to administer or regulate medication, so any changes in medicine during the treatment period will also be obtained at post-treatment. Since the RCT follows the intention to treat principle, participants who receive additional treatment or medication will not be excluded from the statistical analysis. However, the effect of additional treatment and medication will be discussed in the article.

### Provisions for post-trial care {30}

If any participants suffer a serious negative effect of treatment resulting in psychological, physical, or financial loss, the research team is obliged to inform the participants about the Danish Patient Compensation scheme. If necessary, the team will also assist the participants in applying for compensation.

### Outcomes {12}

#### Primary outcome

The primary outcome consists of point differences in anxiety diagnosis and severity measured by Spence Children’s Anxiety Scale (SCAS) [46]. SCAS is a 44-item self-report questionnaire assessing anxiety symptoms of six different anxiety disorders in DSM-IV. SCAS has been validated in a Danish community and clinical sample of children between the age of 7 and 17 years and the results indicated good internal consistency, test-retest reliability and convergent and divergent validity for the questionnaire [47].

#### Secondary outcomes

The secondary outcomes consists of point differences in anxiety diagnosis and severity measured by clinician-review Youth Online Diagnostic Assessment-Child and Parent Versions (YODA) [48]. YODA is an online diagnostic assessment tool that assesses DSM-5 anxiety disorders and specific phobias based on the *Anxiety and Related Disorders Interview Schedule for DSM-5*, which is considered the golden standard [49]. The YODA uses yes/no responses to closed-ended questions, as well as open-ended questions that require written descriptions of cognitions, behaviors and impact on functioning [48]. The YODA is completed separately by the adolescent and the parents, and a clinical psychologist trained in the assessment of adolescent anxiety disorders then reviews and evaluates the responses to determine the diagnosis and symptom severity.

Point differences in anxiety symptoms interference on daily life measured by the self- and parent-reported questionnaire Child Anxiety Life Interference Scale (CALIS) [46]. CALIS [50] is used to measure the impact of youth anxiety on various areas of life functioning such as school, extracurricular activities, family life and friendships. The impact is evaluated separately by adolescents and their parents. In addition, parents rate the degree of impact on their own lives. CALIS has shown satisfactory internal consistency and moderate test-retest reliability [50].

Point differences in depressive symptoms are measured by The mood and Feelings Questionnaire (MFQ) [51]. MFQ is used to screen for depression in youth, both in epidemiological samples and in clinical samples, it is recommended as a self-report screening tool in secondary care [51]. The MFQ is completed separately by the adolescent and a parent. The MFQ has been validated in a Danish population sample of adolescents and shown excellent internal consistency [52].

Point differences in Quality of life is measured by EuroQol-5 Dimension Youth (EQ-5D-5L) [52], a 5-item self-report questionnaire assessing quality of life and self-rated health. The items cover five domains: mobility, self-care, usual activities, pain/discomfort, and anxiety and depression [53].

Other secondary outcomes include outcomes related to overall participant experience, they are therefore not administered at pre-treatment. This includes participant satisfaction with treatment and with system usability, measured by Working Alliance Inventory applied to Internet (WAI-TECH-SF) [54]. WAI-TECH-SF assesses the technical alliance. The WAI-TECH-SF has shown good psychometric properties and excellent internal consistency [54].

Working Alliance Inventory – Short Form (WAI-SF) [55]. The therapeutic alliance will be assessed using the short version of the Working Alliance Inventory. The WAI-SF is a 12-item self-report questionnaire designed to assess the therapeutic alliance with the therapist / online program in a self-guided intervention on three dimensions: therapeutic goals, tasks, and bonds. The WAI-SF will be administered after week 2, 4, 6, 8 and 10 and at post-treatment and be completed by both adolescents and parents.

Client Satisfaction Questionnaire-8 (CSQ-8) [56] is used to measure general satisfaction with the received treatment. The scale has shown high internal consistency and concurrent validity [57].

System Usability scale (SUS) [58] is used to assess the subjective experience of usability of a computer system. A Danish version of the SUS has been validated in a mental health care setting [59].

Negative Effect Questionnaire (NEQ) [60] is a 20-item questionnaire used to monitor the occurrence of negative effects in psychological treatments. NEQ shows acceptable psychometric properties [60].

Engagement with the treatment program will be measured objectively using the number of logins to the treatment program as well as number of words per message sent to the therapist and number of words per text box in the modules. These data are automatically logged in the treatment platform and will be registered for both adolescents and parents.

Completion of the treatment program is defined as completing module 8 for adolescents or being active in the treatment program for all 14 weeks.

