#### iCBT with planned feedback

Participants in the planned feedback iCBT condition will receive written feedback from their therapist on assignments every week. They will also have the opportunity to contact their assigned therapist through messages via a built-in text module within the program and receive asynchronous support if needed.

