### Methods for additional analyses (e.g., subgroup analyses) {20b}

A large number of additional analyses will be conducted. Logistic regression will be used to analyze associations between treatment arms and the secondary outcome YODA (dichotomized) at 3-month follow-up post treatment as well as each of the 20 NEQ items at post-treatment. Linear mixed model regression will be used to analyze associations between treatment arms and the following outcomes through all time points from pre-treatment to 12-month follow-up post treatment: SCAS-C score, CALIS, MFQ score by adolescent, SCAS-P, CALIS, MFQ score by parent, EQ-5D-5L score, CSQ-8 score, and SUS score. Furthermore, linear mixed model regression will be used to analyze associations between treatment arms and WAI-SF at treatment sessions 2, 4, 6, 8, and 10 and at post treatment, and between treatment arms and weekly measures of CAS-8 and S-MFQ. Linear regression will be used to analyze associations between treatment arms and WAI-TECH-SF and engagement at post-treatment, as well as the cost-effectiveness analysis.

Finally, we wish to conduct a post hoc exploratory growth mixture model that can provide trajectories of change in symptoms through the trial across the different sessions and post-measurements.

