### Methods in analysis to handle protocol non-adherence and any statistical methods to handle missing data {20c}

Linear mixed models, which tolerate missing values and minimize the loss of statistical power in case of drop-out, will be fitted using the maximum-likelihood estimation method and based on the intention-to-treat sample. Where relevant in other types of analyses, missing data will be handled using multiple imputation methods.

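### Words per message, one of the three engagement measures, has no value for participants who send no message and scores message length rather than amount of engagement

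*Protocol article*

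**What the plan says.** The engagement outcome is defined in the protocol article under Secondary outcomes. Its first component is a count: "Engagement with the treatment program will be measured objectively using the number of logins to the treatment program". The other two are the "number of words per message sent to the therapist and number of words per text box in the modules". On the source and the persons measured, the article adds: "These data are automatically logged in the treatment platform and will be registered for both adolescents and parents". It does not list the number of messages or the total words written, and it does not say what a participant with no messages scores.

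The analysis is given under Methods for additional analyses {20b}: "Linear regression will be used to analyze associations between treatment arms and WAI-TECH-SF and engagement at post-treatment". For models other than the linear mixed models, section {20c} says: "Where relevant in other types of analyses, missing data will be handled using multiple imputation methods".

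Messaging is a choice in both iCBT arms. For on-demand feedback, "they will have the option to contact the therapist through messages within the program and receive asynchronous support". For planned feedback, which also brings weekly written comments from the therapist, "They will also have the opportunity to contact their assigned therapist through messages via a built-in text module within the program".

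**The concern.** Words per message is most naturally read as a ratio for each participant: words written divided by messages sent. With no messages the ratio is 0/0. An ordinary linear regression leaves such a participant out.

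Whether a participant writes to the therapist is decided after randomisation, and type of feedback is the very factor that was randomised. A contrast among senders is therefore not a contrast of the randomised groups. It can show a difference when message length is unaffected by feedback, or hide one, because the two sets of senders may be different kinds of participant.

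The ratio also measures something other than engagement. It says how long a typical message is, not how much the participant wrote or how often. Someone who writes once at length scores above someone who writes shorter messages every week.

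What is at stake is how the two feedback formats are compared on engagement, a listed secondary outcome that helps explain any difference between them.

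**Working it through.** The article states no figure for engagement, so there is none to reproduce. The check applies the definitions and then shows how far the result depends on non-senders.

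**Which measures are defined for everyone**

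| Measure | Participant who does none of it |
|---|---|
| Number of logins | 0, a valid value |
| Words per message | 0/0, no value |
| Words per text box | 0 if all offered boxes count; no value if only boxes reached count and none was reached. The text does not say which. |

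**Inputs**

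- Arm size: 56 in each iCBT arm (Abstract, Methods).
- Share sending no message: not given; assumed 10% to 50%, in either direction.
- Average among senders: not given; assumed 40 words per message in both arms.

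**Participants without a value** = 56 × share of non-senders

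- 10%: 56 × 0.10 = 5.6, about 6
- 30%: 56 × 0.30 = 16.8, about 17
- 50%: 56 × 0.50 = 28

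**Arm difference, planned minus on-demand.** Among senders it is 40 − 40 = 0. With non-senders coded zero it is 40 × (planned share of senders − on-demand share of senders).

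| Senders, planned / on-demand | No value, planned / on-demand | Senders only | Non-senders coded 0 |
|---|---|---|---|
| 90% / 90% | 6 / 6 | 0 | 0 |
| 90% / 70% | 6 / 17 | 0 | 40 × 0.20 = 8 |
| 90% / 50% | 6 / 28 | 0 | 40 × 0.40 = 16 |
| 70% / 90% | 17 / 6 | 0 | −8 |
| 50% / 90% | 28 / 6 | 0 | −16 |

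On identical data the result is 0 or 16 words depending only on how non-senders are coded, and its sign follows whichever arm has more of them.

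**Length against amount.** Take two participants who both average 40 words per message, one sending 12 messages and the other 3 (assumed). Words per message is 40 for both. Total words are 12 × 40 = 480 and 3 × 40 = 120. The stated measure cannot tell them apart.

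**The case against.** The strongest reply is that engagement as a whole does not lose the least active participants. Logins is the first measure named and has a value for everyone given access; the same section also defines completion for adolescents by module reached or time active. This stands: the fault lies in one measure of three.

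Second, a reader might infer that non-senders will fall mainly in the on-demand arm because the planned arm has weekly feedback to answer. The documents do not support that. Planned feedback is given on assignments and no reply is required. In the on-demand arm, messages are the only therapist support described for that condition. Section {18b} also has the therapist write by chat to any participant inactive for more than 10 days, with no restriction by arm. Non-senders could be commoner in either arm, or equally common.

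Third, a reader might infer that words per text box has the same defect, or that message lengths will be imputed. Neither is stated. An empty box can count as 0 words, and imputation applies only where relevant; a fully logged participant who wrote nothing need not be treated as missing.

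Fourth, the wording may describe only the unit of logging, one word count for each message, with the summary for each participant left to an analysis plan that is not shown. This is a fair reading, and it makes the point conditional. It does not remove it. Message length is what the article names as the measure, and a zero rule in the plan would give non-senders a score but would still not measure amount.

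**Conclusion.** The point holds for words per message, on the condition that it is analysed as an average for each participant, which is the natural reading. In that form it has no value for non-senders, the named regression compares groups selected after randomisation, and the quantity compared is message length rather than amount of engagement.

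Non-senders are foreseeable: messaging is optional in both arms, and section {18b} provides for participants who do not answer chat messages. Their number is unknown. The range of about 6 to 28 of 56 per arm, and the differences of 0 to 16 words in either direction, rest wholly on the assumed shares and the assumed 40 words. They show sensitivity to coding and predict nothing. With equal shares of senders the loss does not differ by arm, though the comparison is still among senders only.

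Severity is minor. This is one component of one secondary outcome, among many additional analyses. Logins is unaffected, words per text box needs only a fixed denominator, and the SCAS and YODA analyses are untouched.

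**What to change.** For all randomised iCBT participants, over the 14 weeks of treatment, define and analyse alongside logins:

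- number of messages sent to the therapist, zero if none;
- total words in those messages, zero if none;
- total words in module text boxes, with unfilled and unreached boxes counted as zero.

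Keep words per message as a description among senders, reported with the number of senders in each arm. Do not impute it, and do not use it for the comparison of randomised arms. Apply the same definitions to the adolescent and parent logs, and fix them before engagement is compared by arm, so that the coding of zeros is not chosen with the result in view.

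This needs no new data collection, since the platform already logs the messages and text boxes automatically. The cost is in the analysis: the totals will be skewed with zeros, so a count model, or linear regression with robust standard errors, is preferable to plain linear regression.
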